### Monitoring

This is a small-scale, single-site, investigator-initiated clinical trial, so a data monitoring committee will not be utilized. The principle investigator will regularly review study data for the occurrence of adverse events (AEs), including moderate to severe effusion, synovitis, local infection, systemic infection, and toxicities. The study will be suspended if more than 1 out of the first 10 patients enrolled in the study group experiences a significant adverse event (SAEs) attributable to the investigational treatment. SAEs are defined (per US FDA) as those that are life threatening, require hospitalization, or result in death, disability or long-term damage. All adverse events (AEs and SAEs) will be recorded in study source documents and will be reported to the University IRB in accordance with federal, state and institutional requirements. Additionally, all AEs and SAEs will be reported with published results.

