### Basic science for clinical study aspects

The principle difference between cell therapies and “minimally manipulated” fat injections is that fat injections are not enzymatically digested. As a result, autologous fat treatments contain both autologous cells, including MSCs [33], and extra-cellular matrix (ECM). Therapies containing ECM are thought to have the following advantages over treatments prepared using enzymatic digestion: (1) preservation of the stromal vascular niche, which allows time-release of the regenerative factors [34]; (2) release of bioactive molecules by exosomes, which have been demonstrated to be significantly greater in mechanically processed fat than enzymatically processed fat [35]; and (3) maintenance of the structural and morphologic unit, which is thought to increase efficacy by making the cells more resilient to the harsh, inflamed conditions in the recipient environment [36]. Enzymatic digestion, which is used to remove the cells from ECM, may remove critical elements involved in tissue repair and may damage the cells, affecting their function and viability. In vitro studies have suggested that cell-containing lipoaspirate obtained without enzymatic digestion may act as a scaffold when administered via intra-articular injection, allowing for the formation of fibrous tissue that provides mechanical support [37]. While non-enzymatic processing produces a lower progenitor cell yield [38, 39], the preserved ECM and growth factors are thought to contribute to the treatments’ overall therapeutic effectiveness.

Preclinical [37] and clinical [40, 41] studies investigating the use of “minimally manipulated” adipose tissue injections have demonstrated preliminary safety, but a number of questions remain unanswered. While ECM has been shown to be beneficial for tissue repair [42] and is commonly used to as a bridging material between new and old tissues [43], these advantages are less applicable to intra-articular fat injections because there are no tissue fragments for the ECM to bridge [44] and because agents injected into the joint tend to be quickly cleared from the body [45]. Most importantly, ECM itself has the potential to produce inflammatory signals [46]. In fact, collagen fragments are known to induce arthritis in animals [47].

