**Fig. 1 Fig1:**
[figure not shown]
Study design flow chart

Male and/or female patients will be randomized to either the HA (Synvic One®) treatment group (*n* = 27) or autologous fat (Lipogems®) treatment group (n = 27). To ensure enrollment goals are met, the investigator will draw from a waitlist of current patients that have expressed interest in participating in clinical trials. We also have IRB-approved flyers/brochures that will be shared with patients and nearby orthopaedic clinics (Additional file 1). Additionally, to improve adherence to the intervention protocol, participant who are allocated to the control group that complete all scheduled follow-up visits will be offered the adipose tissue treatment at the end of their final visit at no cost.

Since our primary aim is to estimate the effect size for future well-powered studies, we estimate the precision around which we can measure the effect. Based on a prior study using similar methods, but comparing WOMAC-A scores among patients receiving placebo to Hylan G-F (a joint lubricant) [54], we assumed standard deviations in the control and treatment groups of 0.66 and 0.67, respectively. With a sample size of 54 (27 per group), we will be able to estimate a two-sided 95% confidence interval within ±0.36 distance from the mean difference. For our secondary aim, we estimated the mean difference we would be able to detect, assuming a similar effect size for HA as was observed for Hylan G-F (μ = − 0.84, σ = 0.67) and found that we would have 80% power to detect a mean difference of − 1.4 in the autologous adipose group with a two-sided Type I error rate of 0.05.

Power was calculated using Pass 14 (Kaysville, UT).

At the treatment visit (day 0), patients will be randomly assigned to receive either a single intra-articular, ultrasound-guided injection autologous adipose tissue (6 ml) or a single intra-articular, ultrasound-guided injection of hyaluronic acid (6 ml). Patients with bilateral OA will be allowed to participate in this study, but only their more painful eligible knee will be treated (as determined by WOMAC-A). To control for possible responder differences between bilateral and unilateral symptomatic patients [55, 56], WOMAC-A for the contralateral knee will be obtained at baseline, 6 weeks, and 6 months (Table 1). If a participant has bilateral OA of equal pain intensity in both knees, the treatment knee will be selected randomly.

**Table 1 Tab1:** Study Calendar

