Timepoint**	Study period				
	Screening	Allocation	Follow-up visits		Close-out
	Day − 21 to 0	day 0	Safety follow-up visit Day 2–7 (inclusive)	Week 6 ± 7 days	Month 6 ± 30 days
Enrolment:					
Eligibility screen	X				
Informed consent	X				
*Focused physical exam*		X	X	X	X
Randomization / Allocation		X			
Interventions:					
*Autologous Adipose Tissue Injection*		X			
*Hyaluronic Acid Injection*		X			
Assessments:					
WOMAC	X	X		X	X
WOMAC-A (contralateral knee)	X	X		X	X
PROMIS-29		X		X	X
Force Plate Analysis (bilateral)		X		X	X
Clinical anchors		X		X	X
Synovial fluid aspiration		X		X	X

The *eligibility screen* includes a detailed physical exam/medical history and pregnancy testing (if applicable). The *focused physical exam* includes Height/weight/vitals, concomitant medications, knee exam, and wound evaluation (if applicable). Only patients that receive the fat treatment will be asked to come in for the safety follow-up. All assessments pertain only to the study knee, unless otherwise indicated

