### Data collection, management, and analysis

Demographics and survey data will be stored using a REDcap database created specifically for the purpose of this study. REDcap has several security features, including off-site backups, an audit trail, secure logins, de-identified data exports, and built-in filtering methods to ensure data quality. Additionally, survey answers (clinical outcome data) will be directly entered into the database by the participants via iPad before they interact with the examining physician. Documentation not included in the quantitative analysis of clinical outcomes will be recorded using traditional source documents (Additional files 2 and 3). These documents will be kept in the participant’s binder and locked in a secure location. All data collection will take place in the clinic.

Only those who require access to the database will be given access. Coding of the variables will be done within the database. A completed data file will be stored by the statistician in the shared folder for the Clinical Translational Science Institute Biostatistics core at USC and will be backed up regularly. The statistician’s access to the database will be limited to de-identified data. Data quality will be assured by range checks for unusual or impossible data values. Data management will include a thorough data cleaning (checking ranges, evaluating distributions) and deriving of variables needed for analysis.

All protocol deviations will be recorded. The same outcome data will be obtained from all participants, regardless of protocol adherence. In order to promote retention and compliance, participants that receive the HA treatment and complete all schedule follow-up visits will be offered the fat treatment at the 6-month (final) follow-up visit at no charge. Imputation will be used if loss to follow-up is uncommon.

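### The article's only numeric suspension rule stops counting at the tenth study-group patient, leaving 17 of the 27 randomized fat patients without a stated trigger

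*Protocol article*

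**What the plan says.** The Monitoring section of the protocol article gives one numeric rule: "The study will be suspended if more than 1 out of the first 10 patients enrolled in the study group" experiences an SAE attributable to the investigational treatment. SAEs are defined there by the usual seriousness criteria. The Methods section plans 27 patients per arm.

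The other safeguards carry no number:
- There is no independent committee: "a data monitoring committee will not be utilized".
- The principal investigator "will regularly review study data for the occurrence of adverse events".
- All adverse events "will be reported to the University IRB in accordance with federal, state and institutional requirements", and the Ethics section adds continuing review by the IRB.
- Table 1 schedules a day 2-7 safety visit: "Only patients that receive the fat treatment will be asked to come in for the safety follow-up".

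HA patients who complete follow-up "will be offered the fat treatment at the 6-month (final) follow-up visit at no charge". Table 1 labels that visit as close-out and shows nothing after it.

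**The concern.** The protocol commits in advance to a count that suspends the study, but the commitment covers only 10 of the 27 patients randomized to the more invasive treatment. A late SAE in one of those 10 still counts. An SAE in patients 11-27 does not, however many there are.

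For those 17 patients, suspension rests on judgement. Several features of the trial make a pre-set trigger more useful than usual. It is unblinded and single-site, it has no data monitoring committee, and the Discussion itself acknowledges the risk of investigator bias. The Background says that earlier studies of this kind of product "have demonstrated preliminary safety, but a number of questions remain unanswered".

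This is not a complaint about a detail left to another document. The article states a threshold, and that threshold has too narrow a window.

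**Working it through.** **Inputs.** The rule is 2 or more events in the first 10 study-group patients (Monitoring). The fat arm has n = 27 (Methods). The documents give no attributable SAE rate, so p = 1%, 2%, 5%, 10% and 20% are assumed. The article states no operating characteristics for its rule, so there is no figure to reproduce.

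The study group is read as the fat arm. If it meant the first 10 patients enrolled overall, only about 5 fat patients would count under 1:1 allocation, and the gap would be wider.

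**Share outside the rule.** 27 − 10 = 17, and 17/27 = 63%.

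**Example that the rule misses.** One event in patients 1-10 and two in patients 11-20 give 3/20 = 15%. The rule sees 1 of 10 and does not fire.

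**Current rule.** P(suspend) = 1 − (1−p)^10 − 10p(1−p)^9. At p = 10% this is 1 − 0.3487 − 0.3874 = 0.2639.

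**Illustrative extension.** Suspend at 2 events within the first 10, 3 within 20 or 4 within 27, computed by exact recursion. The steps at p = 10% are:
- Patients 1-10: 0.2639, as above.
- Patients 11-20: with 0 events so far (0.3487), three or more of the next 10 are needed (0.0702). With 1 event so far (0.3874), two or more are needed (0.2639). The sum is 0.3487 × 0.0702 + 0.3874 × 0.2639 = 0.1267.
- Patients 21-27: not yet suspended with 0, 1 or 2 events at patient 20 has probability 0.1216, 0.2702 and 0.2176. Four, three or two more events among 7 patients are then needed (0.0027, 0.0257, 0.1497). The sum is 0.0003 + 0.0069 + 0.0326 = 0.0398.
- Total: 0.2639 + 0.1267 + 0.0398 = 0.430.

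The last column below is the gain divided by (1 − current). It is the chance of a later rule-based suspension once the first 10 patients have passed, which is 0 under the current rule.

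| Assumed rate | Current rule | Extended count | Gain (points) | Patients 11-27, given first 10 pass |
|---|---|---|---|---|
| 1% | 0.4% | 0.5% | 0.05 | 0.05% |
| 2% | 1.6% | 2.0% | 0.4 | 0.4% |
| 5% | 8.6% | 12.8% | 4.2 | 4.6% |
| 10% | 26.4% | 43.0% | 16.7 | 22.6% |
| 20% | 62.4% | 87.9% | 25.5 | 67.9% |

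**What a suspension would spare.** Each patient gets one injection, so a pause protects only those not yet treated. Weight each stopping point n by its remaining 27 − n patients, and assume that every SAE is seen before the next injection. The extension then withholds on average 0.3, 1.3 and 2.3 more fat injections than the current rule at 5%, 10% and 20%. Multiplied by the rate, that is about 0.02, 0.13 and 0.45 attributable SAEs averted.

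**The case against.** The strongest reply is that the rule is a reasonable early-safety gate and that oversight does not end at patient 10. The investigator keeps reviewing events, the IRB keeps receiving them, and either can halt the study at any count. This stands. A reader might infer that patients 11-27 are unmonitored or that the study could not be stopped for them, and the article does not support that reading. Only a pre-stated trigger is missing. The probabilities above also leave out suspension on judgement, so they describe the rule alone and not the trial's whole protection.

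The full IRB protocol is not shown and might hold further criteria. That is possible, so the point is confined to the article. The Monitoring section, however, gives its rule in full, with no sign of a second stage.

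The benefit is modest and depends on an assumed rate. This also stands: few injections are spared, and no document supports an attributable SAE rate of 10%.

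The example limits are not the only choice. Applying a limit of more than 10% after every patient from 11 to 27 would give 26.9% suspension at a 5% rate and 63.8% at 10%. The sponsor should therefore choose the limits, but this is no reason to stop counting at 10.

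A reader might also extend the point to HA patients later given fat. If all 27 accepted, 44 of 54 fat recipients (81%) would be uncounted, and the running count might seem to cover them at no cost. The documents do not support this. Uptake is not given, treatment comes at the close-out visit, Table 1 schedules nothing after month 6, and the article does not say whether the day 2-7 visit applies to them. A comparable count would need follow-up that the calendar lacks.

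**Conclusion.** The point holds for the 27 randomized fat patients. The article's one numeric rule ignores attributable SAEs in 17 of them, and 3 of 20 can occur without triggering it. Extending the count makes almost no difference if attributable SAEs are rare (0.4 points at 2%) and a material difference only at about 10% or more (16.7 points at 10%, 25.5 at 20%).

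The conclusion rests on assumed SAE rates, on reading the study group as the fat arm, and on example limits. It does not rest on any claim that oversight stops at patient 10, or on any claim about HA patients who receive fat later. It is an inexpensive improvement to consider.

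**What to change.** Keep the first-10 rule unchanged and add one sentence to the Monitoring section that extends it as a running count over the 27 randomized fat patients in order of treatment. For example: suspend for review at 2 attributable SAEs within the first 10, 3 within 20 and 4 within 27. The sponsor should set the limits against a stated maximum acceptable SAE rate. The example limits correspond to about 15% observed (3/20 = 15%, 4/27 = 14.8%).

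Any attributable SAE reported in an HA patient later given fat may be added to the count, without treating that information as comparable or complete.

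For the randomized patients the cost is the sentence and an IRB amendment. The downside is a slightly higher chance of a reversible pause when the true rate is low: 0.5% against 0.4% at a 1% rate, 2.0% against 1.6% at 2%, and 12.8% against 8.6% at 5%.

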### Ethics and dissemination of information

Ethics approval was received from the University of Southern California Health Science IRB (10/9/2017), USC Institutional Biosafety Committee (May 2017) and USC Radiation Safety Committee (September 2017). Continuing reviews and all protocol modifications will be submitted to the USC Health Science IRB through the University iStar System. Because the IRB has determined that this study involves ‘greater than minimal risk’, only the Principal Investigator will be allowed to obtain informed consent. All participants provided written informed consent to participate. Participants will be given a copy of the consent to take home, and an informed consent comprehension assessment will be performed before randomization.

To protect participant confidentiality, samples will not be labeled with information that can be used to directly identify participants. Samples will be labeled with subject identification numbers and only the investigator and IRB-approved study personnel will have access to information linking subject identification numbers to identifiable information. The link between study participants and their study ID numbers will be destroyed (shredded/purged) in accordance with federal regulations when study activities are complete. The final trial dataset will not contain identifiable data and will be available to all investigators listed in the IRB protocol.

There are no additional provisions for ancillary or post-trial care, or for compensation to those who suffer harm from trial participation. However, participants will be informed prior to enrollment that they are responsible for unscheduled visits/interventions and that they are not giving up any legal rights by agreeing to participate in the study (Additional file 4). Once study activities have been completed, results will be published and posted to clinicaltrials.gov.

Personal information will be collected using REDcap, which maintains a secure login and will only be accessible to appropriately delegated study staff, as indicated on the IRB protocol. De-identified data exports will be performed so that statisticians and collaborators may receive data sets without knowledge of personal health information. A de-identified dataset will be stored with the statistician indefinitely. The results of the study, whether positive or negative, will be published. An abstract based on the results may be submitted to an orthopaedics meeting prior to publication. Should the results prove impactful, we may contact the Keck Media Relations Team at USC to assist in developing a press release.

## Discussion

In view of the already widespread use of intra-articular fat injections in the United States, it is critical that randomized, controlled studies aimed at evaluating the clinical efficacy of intra-articular autologous adipose tissue injections for osteoarthritis be performed [68]. This study is the first step towards addressing this unmet need, but it is not without limitations. The most notable limitation of this study is its small size, which is fixed due to funding constraints. However, in order to consider adopting autologous adipose tissue injections as a new therapy for OA, the clinical impact of the treatment would have to be substantial, as autologous fat injects are more costly, carry additional risks, and are more invasive than HA injections. Thus, detecting a small, statistically significant but clinically negligible difference would not advance the treatment of OA.

Another major limitation is the lack of blinding, which predisposes the study to both investigator and subject bias. However, the trauma associated with the removal of adipose tissue from the abdomen is not justified in patients receiving the control (hyaluronic acid). To minimize investigator bias, which is particularly noteworthy given that the study isn’t multi-site, clinical outcomes will be assessed using self-reported measurement tools and responses will be directly entered into a REDcap database by the participants before they interact with the examining physician. Additionally, other response indictors (synovial fluid analysis, fat characterization) will be blinded for analysis.

The removal of synovial fluid presents minimal risk to patients and may help us better understand how autologous fat injections impact the biological environment of the joint. However, puncturing the joint cavity may have clinically important implications. To mitigate this potential limitation, the joint cavity will only be punctured once at the treatment visit. Additionally, outcome assessments will be performed before removing joint fluid and all synovial aspirations will be performed under ultrasound guidance. The number of successful/failed aspirations in each group will be logged and reported in the final published results. While synovial fluid can be challenging to obtain, prior studies conducted by the investigator and others have demonstrated feasibility [69, 70]. Based on the experience of the investigator, > 50% of aspirations are expected to yield analyzable synovial fluid samples.

This study has several strengths. While imperfect, prospective, randomized controlled trials are the gold standard for evaluating treatment effects because they mitigate selection and information bias, as well as confounding variables. Additionally, this study will use WOMAC, which is generally thought to be the gold standard for assessing patient-relevant treatment effects in osteoarthritis [71, 72]. Moreover, WOMAC has been shown to be more responsive than other outcome measures in short-term, small-scale studies [73]. Finally, we will characterize both the treatment (though analysis of discarded adipose) and the biologic response (though the analysis of synovial fluid), which is critical for understanding the treatment bioactivity [74].

Several aspects of this study were changed based on reviewer recommendations. No patients were recruited prior to the implementation and IRB approval of these changes.

## Abbreviations

AE: Adverse event
ECM: Extra-cellular matrix
GLM: Generalized linear models\
HA: Hyaluronic acid
NSAID: Non-steroidal anti-inflammatory Drug
OA: Osteoarthritis
PROMIS: Patient-Reported Outcomes Measurement Information System
SAE: Severe adverse event
WOMAC: Western Ontario and McMaster Universities Osteoarthritis index
